### Clinical definitions

#### Inclusion criteria

##### Acute type A aortic dissection

Referring to patients with clinical manifestations such as chest pain, abnormal electrocardiogram or blood pressure, and confirmed by computerized tomography angiography.

#### Exclusion criteria

##### Iatrogenic aortic dissection

Referring to aortic dissection occurs in cardiac surgery intraoperatively or postoperatively with definite evidence.

##### Bacterial or fungal infections

Presence of clinical manifestations of systemic or local inflammatory response such as fever and elevated inflammatory indicators, and with or without support of bacterial or fungal pathogenic tests.

##### Cushing's syndrome

Referring to patients meeting the diagnostic criteria in clinical practice guideline of Cushing’s Syndrome 2021 [14].

##### Addison's syndrome

Referring to patients meeting the diagnostic criteria of Addison's syndrome [15].

##### Severe preoperative hepatic insufficiency

Referring to patients obtained 10–15 points in the Child-Turcotte-Pugh score.

##### Severe preoperative renal insufficiency

Referring to patients having acute or chronic kidney injury before surgery and meeting the indications for renal replacement therapy.

#### Outcomes

##### Postoperative infection

Referring to infection after cardiac surgery, including deep incisional surgical site infection occurring at the primary chest incision, deep incisional surgical site infection occurring at a secondary incision site, mediastinitis, infectious myocarditis or pericarditis, endocarditis, cardiac device infection, pneumonia, empyema, Clostridium difficile colitis, and bloodstream infection, with or without support of pathogenic evidence [16].

## Statistics

### Sample size

In this study, the SOFA score will be monitored continuously for 4 days after surgery. Our primary hypothesis is that the reduction in SOFA score of patients who will be treated with GC postoperatively would be greater than that in those treated with normal care. Based on our previous study, a decline of 2.87 ± 1.69 between the baseline SOFA score on POD1 and the one on POD 3 was observed in our patients [17]. Assuming a 25% increase in the reduction of the SOFA score in the GC group, a test level of α = 0.1 (bilateral), and a test efficacy of (1-β) = 0.9, it is expected that 96 cases are needed in each group, for a total of 192 cases. An estimate of a 10% dropout rate in these groups indicates that a sample size of 212 cases will be required.

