**Fig. 2 Fig2:**
[figure not shown]
Diagram of interventions

The first dose of MP will be given on the morning of postoperative day (POD) 1 at a dosage of 2 mg/kg/d, followed by another dose with the same dosage 12 h later. On POD 2 and POD 3, MP will be reduced to 1 mg/kg/d and 0.5 mg/kg/d respectively, with 12 h intervals between two injections.

All patients in the control group will receive treatments as usual without the administration of GC. Patients will be required to be supervised by medical personnel when administering the study drug, and their vital signs will be checked regularly in case of emergency.

Strategies to improve adherence to intervention and monitor adherence to procedures will be implemented. Three dedicated research fellows will screen all patients who enter the ICU after surgery. They will be responsible to check if certain candidate meets the study criteria. They will also be in charge of ensuring that intervention will be prescribed based on the protocol. In addition, two independent intensive care specialists will monitor adherence to interventions throughout the study period.

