### Outcomes

The primary outcome will be the difference of Sequential Organ Failure Assessment (SOFA) score on POD 4 compared to baseline (on POD1 before MP administration).

Secondary outcomes will be in-hospital mortality, days of ICU stay; days of hospital stay; duration of mechanical ventilation; tracheotomy; continuous renal replacement therapy; postoperative infection; inflammatory markers on POD 1, 2 and 3; composite endpoint (in-hospital morbidity and mortality or ICU stay over 30 days or tracheotomy).

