### Data analysis

This study will summarize patient disposition, demographic and other baseline characteristics, study drug exposure, safety and efficacy. Statistical analyses will be performed using R, version 3.5.0 (R Foundation for Statistical Computing, Vienna, Austria). Continuous variables will be summarized descriptively based on mean (Mean), standard deviation (SD), median (Median) and maximum (Max) and minimum (Min) values, and comparisons of differences between groups will be based on whether the data meet a normal distribution with a two independent samples t-test or wilcoxon nonparametric test. The categorical variables will be summarized descriptively based on the number of subjects in each category and their corresponding percentage share using the chi-square test, and the Fisher's exact test will be used to analyze the differences between groups if necessary. Kaplan–Meier curves and log-rank test will be used to estimate hospital survival in patients in both arms.

In addition, intention to treat analyses which will include all participants randomly assigned to the study arms regardless of their loss to follow-up or compliance will be implemented. Per-protocol analyses, which include all participants with complete data sets, will also be performed for primary and secondary outcomes. In case of missing data, multiple imputation will be calculated.

An interim analysis will be conducted when the set reaches 50% of the proposed number of patients; if the primary endpoint has been reached and differences exist, the data safety monitoring board will discuss and vote on whether to allow early termination of the study. Unless otherwise specified, α = 0.05 (two-sided test) and *p* < 0.05 was defined as statistically significant.

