### Subgroup analyses

The effect of the treatment among different subgroups: (1) gender, (2) diabetes, (3) The European System for Cardiac Operative Risk Evaluation (EuroSCORE) II, (4) Cardiopulmonary Bypass (CPB) duration, (5) age, (6) high sensitivity C-reactive protein on POD 1 and (7) SOFA on POD 1 will be analyzed. Stratified analysis using a logistic regression or Cox proportional hazards model, as applicable, will be performed. By adding a product term to the model that already contains the treatment and the subgroup factor, the interaction between each subgroup factor and the treatment group will be tested.

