There are a variety of strengths in our study. 1) The effect of GC in patients with aTAAD undergoing surgery is lacking, especially for those undergoing total aortic arch replacement with frozen elephant trunk implantation. Such a patient population is greatly exposed to the risk of SIRS and subsequent deterioration in organ function. This study will be the first RCT to investigate the role GC could play in these patients. 2) Former interventions of GC in cardiac surgery generally adopted a pulse regimen without tapering [7, 20]. The dosage of GC was particularly high (eg. 1 g MP) when given prophylactically before the initiation of CPB. However, benefits of GC to regulate dysregulated inflammation have mostly been observed in critical care studies adopting a mild-to-moderate dose of GC, as we have seen in inflammation-mediated conditions, such as acute respiratory distress syndrome [21–23]. In our study, we will implement an initial dosage of 4 mg/kg/d MP on POD 1 and taper it to 1 mg/kg/d on POD 3. Such a regimen will provide novel evidence on whether sequential and tapered use of GC would be better for patient prognosis. 3) A reduction in the SOFA is a reliable indicator of improvement in organ function and survival potential. Organ failure is one of the most prominent causes of death in surgical patients of aTAAD based on the data from international registry. Unfortunately, accurate definition of organ dysfunction is relatively missing, especially when multiple organs are involved. Previously, we have demonstrated that the SOFA score is associated with and could be used as a good predictor for all-cause in-hospital mortality and a lower SOFA score is linked to a decreased possibility of death after surgery, especially the one on POD 2 and POD 3 [17]. As our primary outcome would look at the difference between the SOFA score on POD 1 and POD 4, we believe such a choice could further elucidate the clinical value of the SOFA score. 4) Multiple biomarkers, such as CRP and IL-6, will be recorded in the research, which has the potential not only to depict a more accurate picture of inflammatory state in patients with aTAAD, but also to monitor and compare the effect of GC on inflammation as part of our secondary outcomes.

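### The plan does not commit to using the POD 2 and POD 3 SOFA scores; a baseline-adjusted repeated-measures model would estimate the same POD 4 effect more efficiently at almost no cost

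*Protocol article*

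**What the plan says.** - **Collection.** Under Sample size: "the SOFA score will be monitored continuously for 4 days after surgery". Table 1 marks SOFA at 24, 48 and 72 h of treatment. The Intervention section starts the clock: "The first dose of MP will be given on the morning of postoperative day (POD) 1". The three marks therefore fall at about POD 2, 3 and 4.
- **Outcome.** Under Outcomes, the primary outcome is the difference in SOFA "score on POD 4 compared to baseline (on POD1 before MP administration". No secondary outcome uses SOFA. The same list does name intermediate days for the laboratory measures: "inflammatory markers on POD 1, 2 and 3".
- **Test.** Under Data analysis, continuous variables are compared by a "two independent samples t-test or wilcoxon nonparametric test". No longitudinal model is mentioned.
- **Subgroups.** The only SOFA value among the subgroup factors is the baseline one: "SOFA on POD 1 will be analyzed".
- **Missing data.** "In case of missing data, multiple imputation will be calculated". The imputation variables are not named.
- **Rationale.** In the Discussion, "a lower SOFA score is linked to a decreased possibility of death after surgery, especially the one on POD 2 and POD 3". The Discussion also expects that some stable patients could be out of the ICU within three days.

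**The concern.** Three post-baseline SOFA scores are collected per patient, and the article promises to use one. The intermediate days are the ones the Discussion cites in support of SOFA as an endpoint, and the planning figures are for the POD 1 to POD 3 decline. Yet neither day appears in a named treatment comparison.

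Two things are at stake. First, precision and handling of missing POD 4 scores: if patients leave the ICU early, or fall within the 10% dropout allowed for, the same patient's POD 2 and POD 3 scores are the best available information on the missing value, and the plan does not ensure that they are used. Second, description: the drug is tapered over POD 1 to 3, and a POD 4 comparison alone cannot show whether a difference appears early, late or fades. An intermediate-day comparison added after unblinding would carry little weight, so it is better fixed beforehand.

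**Working it through.** **1. The plan's own figure.** From Sample size: decline 2.87, SD 1.69, effect 25%, two-sided α = 0.10, power 0.90.

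δ = 0.25 × 2.87 = 0.7175. n = 2(1.645 + 1.282)² × 1.69² / 0.7175² = 95.1, rounded up to 96 per arm. This agrees with the stated 96. Nothing below changes it.

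**2. Assumptions not in the document.** The day-to-day correlation of SOFA is not given. I take four structures for POD 1 to 4: exchangeable with ρ = 0.5 or 0.7, and first-order autoregressive (AR1) with ρ = 0.7 or 0.85. Each is scaled so that the SD of the POD 1 to POD 3 change is 1.69: s² = 1.69² / [2(1 − r13)], with equal variance s² each day.

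**3. Gain from the baseline covariate.**

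- Change score at POD 4: variance 2s²(1 − r14).
- Baseline-adjusted POD 4 score: variance V1 = s²(1 − r14²).
- Ratio: (1 + r14)/2.

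**4. Further gain from POD 2–3 when a fraction m of POD 4 scores is missing at random.** Let V123 be the POD 4 variance given POD 1, 2 and 3.

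- Baseline only: V1 / [n(1 − m)].
- With POD 2–3: [V123/(1 − m) + V1 − V123] / n.
- Ratio: 1 − m(1 − R), where R = V123/V1. I use m = 0.10.
- V123 is s²[1 − 3ρ²/(1 + 2ρ)] if exchangeable and s²(1 − ρ²) if AR1.

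| Structure | r14 | Change-score variance | V1 | Cut from baseline covariate | V123 | R | Further cut from POD 2–3 |
|---|---|---|---|---|---|---|---|
| Exchangeable 0.5 | 0.500 | 2.856 | 2.142 | 25% | 1.785 | 0.833 | 1.7% |
| Exchangeable 0.7 | 0.700 | 2.856 | 2.428 | 15% | 1.845 | 0.760 | 2.4% |
| AR1 0.7 | 0.343 | 3.679 | 2.471 | 33% | 1.428 | 0.578 | 4.2% |
| AR1 0.85 | 0.614 | 3.972 | 3.205 | 19% | 1.428 | 0.446 | 5.5% |

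With no missing scores (m = 0) the last column is zero: the repeated-measures model then gives essentially the baseline-adjusted POD 4 estimate.

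**5. Why POD 4 should stay primary.** The baseline-adjusted mean of POD 2–4 has 0.55 to 0.61 of the variance V1. Power, by normal approximation with 96 per arm and two-sided 0.05, is Φ(effect / √(2V/96) − 1.96):

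- POD 4 alone, effect 0.7175: 79% to 93%.
- POD 2–4 mean, full effect on every day: 96% to 99%.
- POD 2–4 mean, effect building up by thirds (average effect 2/3 × 0.7175 = 0.478): 71% to 86%.

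The average therefore gains or loses power depending on how early the effect appears, which the document does not say.

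**The case against.** The strongest case against is that nothing here is wrong. One prespecified day is a legitimate primary endpoint, and POD 4 follows the whole three-day course. Supportive longitudinal analyses are often left to an analysis plan, and none is shown. This stands, and it limits the point to an optional improvement of the stated method.

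The gain that is specific to the POD 2–3 scores is small, and it is measured against an analysis using baseline only, which the protocol does not specify. If the planned imputation includes those scores, most of that gain is already secured. This also stands. The larger gain comes from the baseline covariate, which could be had from a simple adjusted analysis of POD 4 alone. One mixed model delivers both.

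A mixed model also assumes missing at random, and death is not an ordinary missing score. That is true, and the model does not solve it.

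A reader might go further than the documents allow in four ways:

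- *The POD 2–3 scores are excluded from every comparison.* The general sentence on continuous variables and the unspecified imputation could both take them in. The text is silent; it does not exclude them.
- *The protocol calls POD 2 and POD 3 the most prognostic days.* It says that the link holds especially for them. It does not say that POD 4 was examined in the earlier study.
- *The team's data tie the expected effect to POD 3.* Only the decline and its SD come from data; the 25% effect is an assumption.
- *The most precise SOFA contrast is thrown away.* The POD 2–4 mean answers a different question, so its smaller variance is not a gain for the question asked.

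**Conclusion.** The point holds as a low-cost efficiency improvement of minor weight. SOFA is collected on three post-baseline days, the named outcomes use one, and the plan does not commit to the other two, even where a POD 4 score is missing. The primary test remains valid and the stated sample size is unaffected.

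For the POD 4 contrast, the expected gain is about 15–33% less variance from the baseline covariate. The POD 2–3 scores bring a further 2–6% if 10% of POD 4 scores are missing at random, and nothing material if POD 4 is complete. These ranges rest on assumed correlations of 0.5 to 0.85, equal variances across days, and an SD borrowed from the POD 3 change. They should be read as an order of magnitude.

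**What to change.** Keep POD 4 as the primary time point. Replace the single-day test by one linear mixed model of the POD 2, 3 and 4 SOFA scores with arm, day, arm-by-day, the pre-drug POD 1 SOFA as covariate (slope allowed to differ by day, as the calculation assumes) and an unstructured covariance. Take the POD 4 arm contrast as the primary estimate. Report the POD 3 contrast, and optionally the POD 2–4 average, as supportive only. If multiple imputation is kept for any SOFA analysis, name the POD 1, 2 and 3 scores among its predictors. State a separate rule for deaths before POD 4.

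Cost: a few sentences in the Data analysis section and one model in R, with no new data or patients. The downsides are a slightly more complex model, reliance on missing at random, and the need to label the extra contrasts clearly. The change should be made before any unblinded comparison is seen, including the planned interim analysis.

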**Methods:**

This study will be an investigator-initiated, prospective, single-blind, randomized, single-center study. Subjects with confirmed diagnosis of aTAAD undergoing surgical treatment will be enrolled and 1:1 randomly assigned to receive either glucocorticoids or normal treatment. All patients in the glucocorticoids group will be given methylprednisolone intravenously for 3 days after enrollment. The primary endpoint will be the amplitude of variation of Sequential Organ Failure Assessment score on post-operative day 4 compared to baseline.

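### The 90% power is calculated from the POD 1 to POD 3 change in SOFA, but the primary endpoint is the POD 1 to POD 4 change, so it is unsupported for the endpoint tested

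*Protocol article*

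**What the plan says.** The endpoint is the same wherever it is defined. The abstract gives it as the "amplitude of variation of Sequential Organ Failure Assessment score on post-operative day 4 compared to baseline". The Outcomes section fixes both ends of the interval: "The primary outcome will be the difference of Sequential Organ Failure Assessment (SOFA) score on POD 4 compared to baseline (on POD1 before MP administration" (baseline is the score before the first dose on POD 1). The Discussion repeats that "our primary outcome would look at the difference between the SOFA score on POD 1 and POD 4".

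The Sample size section uses another interval. It says that SOFA will be followed for 4 days and then takes its planning figures from the earlier study: "a decline of 2.87 ± 1.69 between the baseline SOFA score on POD1 and the one on POD 3 was observed in our patients". The treatment effect is a proportion of that decline: "Assuming a 25% increase in the reduction of the SOFA score in the GC group". With a two-sided α of 0.10 and 90% power, the section arrives at 96 per group and 192 in total, and at 212 after an allowance for dropout.

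The article gives no mean or SD for the change to POD 4, and does not say that the POD 3 figures stand in for it.

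**The concern.** The result of the calculation depends on two numbers: the mean decline, because the effect is set at 25% of it, and the SD of the decline. Both are POD 3 figures. A further day can move either one. If patients keep recovering, the mean decline grows and the assumed absolute effect grows with it. If patients diverge, the SD grows and the standardised effect shrinks.

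The article also gives reasons not to treat the two days as interchangeable without comment. The study drug is given on POD 1, 2 and 3, so POD 3 lies within the treatment course and POD 4 after it. The Discussion notes that some stable patients may leave the ICU in 3 days.

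What is at stake is how the primary result is read. A null result is commonly weighed against the stated power. If the 90% was worked out for another interval, readers cannot tell how much weight a null result at POD 4 deserves.

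**Working it through.** **Inputs from the Sample size section**
- Mean decline, POD 1 to POD 3: 2.87
- SD of that decline: 1.69
- Effect: 25% of the decline, so Δ = 0.25 × 2.87 = 0.7175 points
- Two-sided α = 0.10 (z = 1.645); power 0.90 (z = 1.282); 1:1 allocation

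**Step 1: reproduce the plan's figure.** With the normal approximation,

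n per group = 2 × (1.645 + 1.282)² × SD² / Δ² = 2 × 8.564 × 2.856 / 0.5148 ≈ 95.02, rounded up to 96.

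The t-test solution is 95.7, also 96. At 96 per group the t-test power is 90.1%. The plan's number is reproduced exactly, and from the POD 3 inputs.

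**Step 2: what would have to hold at POD 4.** The standardised effect is 0.25 × mean / SD, so at a fixed n and α the power depends only on the ratio of mean decline to SD. The POD 3 ratio is 2.87 / 1.69 = 1.70. The 90% carries over to POD 4 only if the POD 4 ratio is also about 1.70. With an SD of 2.0, for example, the mean decline would have to be about 1.70 × 2.0 = 3.4. The documents give neither number.

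**Step 3: illustrative range.** The POD 4 values below are assumptions, not figures from the documents. Powers are for a two-sample t-test with 96 per group and Δ = 0.25 × mean. The last column is included because the Data analysis section sets a two-sided α of 0.05 unless otherwise specified.

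| Mean decline | SD | Δ | Δ / SD | Power, α 0.10 | Power, α 0.05 |
|---|---|---|---|---|---|
| 2.87 (plan, POD 3) | 1.69 | 0.718 | 0.425 | 90% | 83% |
| 2.87 | 2.0 | 0.718 | 0.359 | 80% | 70% |
| 3.5 | 2.0 | 0.875 | 0.438 | 92% | 85% |
| 4.3 | 2.07 | 1.075 | 0.519 | 97% | 95% |

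The second row holds the decline at its POD 3 value while the spread widens. The fourth lets the decline continue at its earlier pace (2.87 × 1.5 ≈ 4.3) and the SD grow as it would with independent daily increments (1.69 × √1.5 ≈ 2.07). That is a rough model for a bounded score and serves only to mark a favourable case.

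**The case against.** The strongest reply is that nothing has been miscalculated. The input is labelled openly as a POD 3 figure. It is the same score with the same POD 1 baseline in the group's own earlier patients, one day short of the endpoint. Taking a neighbouring day as a proxy can be reasonable, and a condensed article need not argue every planning choice. This stands as far as it goes: the arithmetic is right, and the choice of proxy is not in itself an error. It does not supply the missing link, because the article states the endpoint, the inputs, α, power and n, and the inputs and the endpoint do not match.

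A reader might infer that the trial is underpowered. The documents do not support that. The low figure in the table comes from widening the SD while freezing the mean. If both are extended by a day, power rises above 90%. There is no POD 4 mean or SD to decide between these cases.

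A reader might also take the Discussion's remark that "a lower SOFA score is linked to a decreased possibility of death after surgery, especially the one on POD 2 and POD 3" as evidence on the planning inputs. It concerns the score's level as a predictor of death and says nothing about the mean or SD of a change. Nor does the mismatch alter the interim analysis, since half of the proposed number of patients is the same count whichever day supplied the SD.

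Finally, every power at α 0.10 depends on that level being the one used for the primary test. The difference between the Sample size and Data analysis sections on α is a separate matter. It does not remove this one, but it affects every figure that is restated.

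**Conclusion.** The point holds in a limited form. The 96 per group and the 90% power follow correctly from the POD 1 to POD 3 decline, while the primary endpoint is consistently the POD 1 to POD 4 change. The stated power is therefore unsupported for the endpoint tested. It is not shown to be wrong, and the direction of any error is unknown.

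Under the assumed POD 4 values, power at 96 per group runs from about 80% to about 97% at two-sided α 0.10, and from about 70% to about 95% at two-sided α 0.05. These ranges reflect the values chosen for illustration and are not estimates of the trial's power. They also rest on the plan's assumption that the effect is 25% of the control decline. This is a gap in the justification of a headline design figure, worth correcting because it is cheap to correct.

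**What to change.** In the Sample size section:

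- If the earlier cohort has POD 4 scores, replace the POD 3 figures with the mean and SD of the POD 1 to POD 4 change, and restate the power that 96 per group gives.
- If it does not, say that the POD 3 figures are used as a proxy for POD 4, and give the power over a range of mean decline and SD. Alternatively, re-estimate the SD from blinded pooled POD 4 data during the trial and restate the power.
- In either case, do the calculation at the α that will be used for the primary test, and name that α.

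The enrolment target and the POD 4 endpoint stay unchanged. The cost is one recalculation and a sentence or two of text, with no extra patients or visits. The article does not say whether the earlier cohort recorded POD 4 scores, so the second route may be the one available. The restated power may turn out less favourable than 90%.

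### The sample size assumes a two-sided α of 0.10, but the analysis section tests at two-sided 0.05; if 0.05 governs the primary comparison, 96 per arm gives about 83% power, not 90%

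*Protocol article*

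**What the plan says.** The Sample size section bases the planning on the centre's own earlier study, in which "a decline of 2.87 ± 1.69 between the baseline SOFA score on POD1 and the one on POD 3 was observed". The effect is set relative to that decline: "Assuming a 25% increase in the reduction of the SOFA score in the GC group". The error rates are "a test level of α = 0.1 (bilateral), and a test efficacy of (1-β) = 0.9", and the result is that "it is expected that 96 cases are needed in each group, for a total of 192 cases". After an allowance for 10% dropout, "a sample size of 212 cases will be required".

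The Data analysis section gives a different level: "Unless otherwise specified, α = 0.05 (two-sided test"), with p below 0.05 defined as statistically significant. For continuous variables it names a two-sample t-test or a Wilcoxon test. It also plans an interim analysis at half the planned number of patients, after which the monitoring board may vote on early termination if a difference is present on the primary endpoint.

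The Outcomes section defines the primary outcome as the SOFA score on postoperative day (POD) 4 compared with POD 1 before study drug. It gives no significance level.

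**The concern.** The trial appears to be sized for one test and analysed with a stricter one. The Sample size section mentions 0.10 only as an input to the calculation, while the section that says how results will be judged gives 0.05.

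Two things are at stake. The first is the power: 90% belongs to a test at 0.10 and does not carry over to a test at 0.05. The second is the decision rule. A primary p-value of 0.07 would be positive under one section and negative under the other, and the interim decision inherits the same doubt. If the level is settled only once results are known, the choice can no longer be shown to be independent of them.

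**Working it through.** **Inputs, all from the protocol article**
- Control decline 2.87, SD 1.69 (Sample size)
- Difference: 0.25 × 2.87 = 0.7175 points; standardised 0.7175 / 1.69 = 0.425 (Sample size)
- Power 0.90; α 0.10 two-sided (Sample size) or 0.05 two-sided (Data analysis)
- Allocation 1:1 (Overview); 96 per arm, 192 in total, 212 enrolled (Sample size)

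**Step 1. Reproduce the plan's figure.** Per arm, n = 2 (z₁₋α/₂ + z₀.₉₀)² (SD / difference)², where (1.69 / 0.7175)² = 5.548.
- Two-sided 0.10: 2 × (1.645 + 1.282)² × 5.548 = 95.02, rounded up to **96**. The t-test version gives 95.7, also 96. The plan's figure is reproduced.
- Two-sided 0.05: 2 × (1.960 + 1.282)² × 5.548 = 116.6, so 117 (118 by t-test). Not reproduced.
- One-sided 0.10: 73. Not reproduced.
- One-sided 0.05 uses the same z-value as two-sided 0.10, so it also gives 96.

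The 0.10 is therefore not a misprint for a two-sided 0.05; the number was calculated with it.

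**Step 2. Power of the same design at each level.** With 96 per arm, the expected test statistic is 0.425 × √(96/2) = 2.94.

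| Evaluable per arm | α (two-sided) | Normal approximation | t-test |
|---|---|---|---|
| 96 | 0.10 | 90.3% | 90.1% |
| 96 | 0.05 | 83.7% | **83.3%** |
| 106 (all 212 evaluable) | 0.05 | 87.1% | 86.8% |

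At 0.05 the risk of missing the assumed effect is 100 − 83.3 = 16.7%. Even with no dropout the power stays below 90%. If the Wilcoxon test were used on normally distributed data (relative efficiency about 0.955), power at 96 per arm and 0.05 would be about 82%.

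**Step 3. What 90% at two-sided 0.05 would require.** 117 per arm is 234 evaluable, and 234 / 0.9 = 260 enrolled. With 118 per arm, 236 / 0.9 = 262.2, so 263.

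**Step 4. Dropout allowance.** 192 × 1.10 = 211.2, rounded up to 212, which is the plan's figure. But 10% loss from 212 leaves 212 × 0.9 = 190.8, just under 192. Retaining 192 needs 192 / 0.9 = 213.3, so 214. At 190.8 evaluable (95.4 per arm), t-test power at 0.10 is 89.9% instead of 90.1%.

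**The case against.** The best defence is the qualifier that opens the analysis rule, which lets another level apply where one is specified. The Sample size section states 0.10 directly alongside the primary hypothesis and is the only place where another level appears. If it counts as the specification, the 90% is correct and there is no power shortfall. This defence stands to the extent that it makes the 83% conditional. A reader might infer that the design simply lacks its stated power, or that the sample size arithmetic is wrong. The article supports neither inference: 96 follows correctly from its inputs, and the fault is a conflict between two sections. What the defence does not do is remove the conflict. The 0.10 is offered as a planning input, and no sentence makes it the level at which the primary result will be judged.

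It can also be said that 83% is still above the customary 80%, and that the intention-to-treat analysis with multiple imputation covers all randomised patients. Both are fair and limit the seriousness. But even 212 fully evaluable patients give only 86.8% at 0.05, so the stated 90% is not rescued.

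A further inference would be that planning on POD 3 data for a POD 4 endpoint lowers power more. The mismatch is there, but its direction is unknown. The effect is defined as a share of the decline, so a larger POD 4 decline could offset a larger SD, and the article gives neither a mean nor an SD for POD 4. Nor can one assume that adjusting for baseline SOFA would win back the lost power, because the article gives no baseline correlation from which to calculate it.

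**Conclusion.** The point holds as an unreconciled conflict over the primary significance level. If two-sided 0.05 governs, which is the natural reading of the Data analysis section, power is about 83% (83.3% by t-test, 83.7% by normal approximation). If 0.10 governs, power is 90%, but the primary test runs at twice the false-positive rate the analysis section sets, undeclared. The text needs correction in both cases.

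The 83% assumes 96 evaluable patients per arm, a true difference of 0.7175, an SD of 1.69 carried over from POD 3 to POD 4, and no α spent at the interim look. Any α spent there would reduce it further. The dropout slip is real but minor: it moves power by about 0.2 percentage points and does not carry the finding.

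**What to change.** Before any interim or unblinded look at the data:

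1. Name one significance level for the primary SOFA comparison, in the same words, in the Sample size and Data analysis sections. Two-sided 0.05 is preferable, since it is already the general level.
2. Restate the power accordingly, for example: *96 evaluable patients per arm give about 83% power for a difference of 0.72 points, SD 1.69 from POD 1 to POD 3 data, at two-sided 0.05.* If 0.10 is intended, say openly that it is the primary decision level and justify it.
3. Note beside the calculation that the planning data end at POD 3 while the endpoint is at POD 4, and that the effect of this on power is not known.
4. Minor: state that 212 enrolled leaves about 190 evaluable after 10% dropout, or change the target to 214.

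Items 1 to 3 are wording changes to the protocol, carried into any analysis plan, and need no extra patients. The cost is that, under 0.05, the declared power becomes less favourable. Only if the investigators wish to keep 90% at two-sided 0.05 would enrolment have to rise, to about 260.
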